##### Sample Size and Sampling for the Process Evaluation

All teachers involved in teaching life skills are included, health advisors and a sample of activists will be invited to take part in the study. Additionally, A sample of first year students from the Faculty of Health Sciences and the Faculty of Economy and Management, both at the UCM, will be systematically selected through a stratified random sampling procedure strategy from the cohort's participants list within faculty and gender groups, as well as consideration of a number of interviews to achieve saturation, which is expected to range between 6 and 12 per gender and per faculty (23–25). The same procedure will be applied to select participant from the activists' groups at both Faculties of the UCM.

##### Study Procedure

Inclusion criteria:

**Activists**

Attending second to fourth year for all courses, and second to sixth year for medicine at the UCM.Actively engaged in sensitizing activities.

**Health advisors**

Holding a valid fulltime working contract at the UCM.Formally assigned to offer STIs screening, counseling and testing services at the UCM.

**Teachers**

Holding a valid fulltime working contract at the UCM.Assigned to teach the life skills discipline in the current academic year.

**Program users**

First year university students from UCM.Being aged 16 to 25 years old.

###### Technic and Instruments of Data Collection.

The process evaluation research will use different techniques and instruments of data collection (see Table 1). Summarizing, face-to-face structured interviews will be applied to collect data from program implementers. The interviews will follow a structured interview guide (Appendix 4a–c). The instruments will be pre-tested for language adjustment, and revision will be performed if needed.

Observations and checklists will also be used to assess provision of curricular lessons and delivery of awareness activities. Tracking of program materials, training records, lessons, awareness activities and screening records will be used to capture data regarding reach, dose delivered and dose received, including fidelity and recruitment. Moreover, face-to-face structured interviews (Appendix 4d) and focus group interviews (Appendix 4e) will be conducted with a sub-sample of users to assess participants' responsiveness to the intervention.”

###### Collection of Data.

The first interview will be done to assess how activists engage in sensitization activities, what they think about the usefulness of the program for themselves and for other students, and what they think about improvement of the intervention. The interview will be conducted face-to-face using a structured guide (Appendix 4a).

The second interview is designed for teachers of the life skills subject, to learn more about the area of their training, how they were selected to teach the subject, how long they have been working as university lecturers, what their experience with SRH contents is (including number of trainings relative to the field), how they evaluate the attendance and participation of students to lessons of this subject. The interview will be guided by a structured form (Appendix 4b).

The last interview among the implementers will be done among the health advisors; open-ended questions (Appendix 4c) will be used to seek data regarding their area of training, experience and skills as health advisor (including trainings on SRH), what they think about utility of their activities to students, what sort of problems students usually report when they visit them, what the main challenges in daily work are, and what they propose to improve the program.

All implementers will be asked to fill in a checklist and record sheets, in order to evaluate the reach, dose delivered and received, recruitment and fidelity of the program implementation. During the interview process, the conversations will be recorded and subsequently transcribed to limit possible bias and ensure natural information provided by the participant; also the interviewers will take notes during the interaction.

Additionally, a selected sample of program users will be asked to attend a face-to-face interview. The interview will be administered using a structured interview guide (Appendix 4d). At the end of the follow-up period, focus group interviews are planned, aiming to explore experiences, motivations and barrier of students to engage in recommended sexual health behaviors. The interview will be administered by study data collectors using a structured interview guide (Appendix 4e).

Focus group interviews will enable to access person's experiences, beliefs, opinions, values and desires. The sampling procedure will follow the same design as described above. Hence, from the list of participants studying at the Faculty of Health Sciences and Faculty of Economy and Management at the UCM, subjects will be randomly selected within gender groups and asked to take part of the group interview, until the sample size is completed (four groups of 6–12 participants) and saturation is achieved.

Participants will receive written and oral information about the group interview details (Appendix 4e), including assurance regarding ethical issues (anonymity and confidentiality); the participant will be given enough time to decide. If he/she decides to take part in the focus group interview, the data collector will schedule the date and time for interview according to the participant preference.

Written informed consent process will be conducted with all participants before the interview. Confidentiality and anonymity will be ensured to the participant, thus, the interview contents will be labeled using codes, and it will take place in an area free from distractions and at the times and location that are considered suitable by the participants, for instance, at the faculty in a closed classroom. The focus group interview may last 1.5–2 h and will be carried out within gender and faculty specific groups. Hence, four focus group interviews are expected to be held: each gender group within each of the two faculties.

All interview sessions will be recorded and transcribed afterward. Two researchers will be present, one as a moderator and another one as observer. The observer will not be allowed to contribute with any idea, his/her task will be to take notes and record the sessions in as much detail as possible. The participants will be explained the procedure before the interview starts. All focus group interview participants will be compensated for transport, and snacks will be shared at the end of the interview.

##### Data Analysis

Quantitative data will be processed and analyzed using SPSS version 25 (Statistical Package for the Social Sciences); descriptive statistics and proportions will be reported.” Qualitative data will be managed and analyzed using the NVivo software. A combination of thematic method and narrative analysis (26–31) will be performed. On the one hand, the thematic approach will consist of transcription of the recorded interviews, coding, identification of categories and building theme maps where each category fits and interpret the findings based on themes that represent experiences, beliefs, attitude and other constructs regarding the behavior.

On the other hand, the narrative approach will consist of understanding the content and structure of the transcribed stories through reading and re-reading the transcriptions, identify crucial constructs (feeling, reactions, accounts, excuses, explanations), writing a summary addressing the main elements such as beginning, middle and the end of the narrative. The transition between themes will be captured and thematic connection of ideas will be developed based on the content of the story, finally comparison among different views of participants regarding the intervention will be presented.

#### Effect Evaluation

The effect evaluation including its indicators and methods are summarized in Table 2. The main questions to be answered are: (a) What changes in behavior and individual-level determinants occurred, and (b) To what extent is the students use correctly and consistently condom, use screening services regularly as well as the prevalence and incidence of STI/HIV changed? The hypotheses are: (a) The program is effective in positively changing personal determinants (Knowledge, risk perception, attitude, self-efficacy, skills and subjective norms) associated with unprotected sexual intercourse behavior among university students and regular use of screening services for STI/HIV; (b) The program is effective in reducing cyclical transmission of STI/HIV among university students; (c) The program is effective in increasing the use of STI screening services; (d) The program is effective in increasing reported rate of condom use among participants.

**Table 2 T2:** Effect evaluation overview for the “Take the opportunity to listen and to be listened to!”

**Outcome**	**Question/Prepose**	**Indicator**	**Methods**
Individual-level determinants of safe sex	What changes in individual-level determinants of safe sex occurred?	Likert-type response scales means and standard deviation.	Questionnaire to a sample of first year university students from intervention and control group.
Individual-level determinants of STI/HIV counseling and testing services use	What changes in individual-level determinants of STI/HIV counseling and testing services use occurred?	Likert-type response scales means and standard deviation.	Questionnaire to a sample of first year university students from intervention and control group.
Reported correct and consistent use of condom	To what extent the students use correctly and consistently condom?	Proportion of students who express correct use of condom and/or report use of condom.	Questionnaire to a sample of first year university students from intervention and control group.
Use of STI/HIV counseling and testing services	To what extent the students use STI/HIV screening services regularly?	Proportion of students who express regular use of screening services. Proportion of students who regularly use Screening services.	Questionnaire to a sample of first year university students from intervention and control group. Analysis of counseling and testing services records.
Occurrence of STI/HIV	To what extent the prevalence and incidence of Syphilis, HIV and reported general symptoms of STI changed.	Prevalence and incidence of Syphilis/HIV or symptoms of any STI.	Analysis of counseling and testing services records, including test results.

A cohort study applying a quasi-experimental non-equivalent control group design with pre-post approach will be used since the intervention is ongoing and by its nature, the use of a full experimental design is unjustifiable. Students registered for the first year, willing to take part in this study, will fill in the questionnaire at enrollment, post intervention and at follow up. The participants will be encouraged to visit a health advisor to undergo an STIs screening through clinical and testing examination. Considering that the prevalence of STI in general is high among young adults, and the primary outcome of the intervention is (determinants of) behavior change, all students, no matter their STI/HIV state, will be enrolled in the cohort and followed-up for 6 months. Students enrolled at UCM will be exposed to the full program, and students from UniLicungo will only receive information from research team and teachers to visit STI counseling and testing office.

The main aims of the cohort are: To analyze changes in behavior and individual-level determinants that in turn influence unprotected sex behavior and use of STI/HIV screening services among university students in Beira city after exposure to the intervention, as well as to monitor cyclical transmission of STIs including HIV among first year university students in Beira at 3 and 6 months after setting up the cohort. During the follow-up period there will be regular consultations, every 3 months for STIs/HIV screening and questionnaire self-filling. Treatment will be offered at the health center to students that are diagnosed with an STI, and the participant will not be withdrawn from the cohort.

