##### Study Procedure

Data collection will be performed by three data collectors after being trained in a 2-day session. The training will focus on study aims, how to obtain informed consent, how to approach the participants and how to distribute and collect the questionnaires. The data will be collected through a self-administered structured questionnaire (see Supplementary File, Appendix 3) with closed-ended questions in Portuguese, the official language of Mozambique. The questionnaire is developed based on the change objectives (see matrices in Supplementary File), using Likert-type response scales (33) and guided by recommendations of Fishbein & Ajzen (34). One or two days before data collection, courses' coordinator of each selected class will explain about the study and invite students to take part. Confidentiality will be ensured, and codes will be used to identify each participant's questionnaire including the study participant's identification card.

Informed consent will be obtained collectively before questionnaire distribution to the class though each candidate will freely decide and sign the consent form. The data collection process will take place in classrooms. The same questionnaire will be administrated to the study participants three times (time 0 at enrolment visit; time one after 3 months of program implementation and time 2 6 months after). At the time one and two, participants will be asked to respond only to questions regarding intersexual relationship (section 2) and questions addressing behavioral outcome 1 and 2 (section 3 and 4, respectively).

During the time of filling in questionnaires, students will not be allowed to chat or to look at classmates' answers. Thus, in case of doubt, students will be advised to ask the data collector for clarification. After a given time for completing, the data collector will recollect the questionnaires, give a study participant identification card, and recommend her/him to visit the health advisor office for STIs counseling and screening within the following days.

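### STI/HIV occurrence is read from voluntary testing records that the programme aims to increase, so the comparison for hypothesis (b) can be biased in either direction and cannot carry an effectiveness claim

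*Protocol article*

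**What the plan says.** All places are in the Protocol article.

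- **Outcome and source.** The last row of Table 2 (Effect Evaluation) has the indicator "Prevalence and incidence of Syphilis/HIV or symptoms of any STI" and the method "Analysis of counseling and testing services records, including test results". No other source is named for this outcome.
- **How students enter those records.** The design paragraph under Effect Evaluation says "The participants will be encouraged to visit a health advisor to undergo an STIs screening through clinical and testing examination". Under Study Procedure, data collectors "recommend her/him to visit the health advisor office for STIs counseling and screening within the following days". The design paragraph also announces consultations every 3 months for screening and questionnaires, but nothing makes attendance a requirement.
- **What the programme does to attendance.** Hypothesis (c) reads "The program is effective in increasing the use of STI screening services". Step 3 describes four activist sessions, one purpose of which is to raise use of the screening service. According to the design paragraph, UniLicungo students receive only information from the research team and teachers about the testing office.
- **What is to be concluded.** Hypothesis (b) reads "The program is effective in reducing cyclical transmission of STI/HIV among university students". The paragraph on the aims of the cohort is softer and speaks of monitoring cyclical transmission at 3 and 6 months.
- **Safeguard.** The Discussion lists ascertainment bias among the possible pitfalls and expects the control-group pre-post approach to control most of them.

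**The concern.** An infection is seen only if the student visits the health advisor. The programme is designed to increase those visits, and UCM has a component for this that UniLicungo lacks. So if hypothesis (c) is true, the chance that an infection is detected differs between the arms, and the programme causes the difference after baseline. The data for hypothesis (b) then mix a change in infection with a change in who is tested.

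A pre-post comparison with a control group removes stable differences between the two universities. It does not remove one that the intervention creates during follow-up. The study could therefore report a benefit or a harm on STI/HIV occurrence that reflects only testing behaviour. The number of new infections expected in 6 months is also likely to be small, and the sample size was not chosen with infections in mind.

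**Working it through.** **Inputs from the document.** Sample Size and Sampling: 95% confidence, half-width 0.15, Cohen's d 0.2, 687 participants, 20% dropout, 824 recruited, 412 per university. Follow-up is 6 months. Introduction: syphilis prevalence 2.2 to 10.3% (age 15–24, sub-Saharan region) and HIV prevalence 16.3% (Sofala, age 15–49).

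**Assumptions.** Testing shares, true relative risks (RR) and incidence are not in the document. They are illustrative, and ranges are shown.

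**1. The plan's own figure.** n per group = (1.95996/0.15)² × (2 + 0.2²/4) = 170.73 × 2.01 = 343.17. The total is 686.3, rounded up to 687, which reproduces the stated figure. Then 687 × 1.2 = 824.4, stated as 824. This is the precision of a standardised mean difference for determinants and behaviour. No infection rate enters it.

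**2. Untested students counted as negative.** Recorded share = p × t, with p the true prevalence and t the share tested. Apparent RR = true RR × (t at UCM / t at UniLicungo).

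No true effect, p = 10%, testing 80% v 50%: 8% v 5%, RR = 1.6.

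True RR 0.80, UniLicungo prevalence 10.3%, 412 per arm:

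| Tested, UCM v UniLicungo | Detected, UCM v UniLicungo | Apparent RR |
|---|---|---|
| 40% v 40% | 13.6 v 17.0 | 0.80 |
| 90% v 80% | 30.6 v 33.9 | 0.90 |
| 60% v 40% | 20.4 v 17.0 | 1.20 |
| 60% v 30% | 20.4 v 12.7 | 1.60 |

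The sign reverses once the ratio of testing shares exceeds 1/true RR: 1.25 for RR 0.8, 1.43 for 0.7 and 2.0 for 0.5.

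**3. Tested students only.** Observed prevalence = p·tᵢ / (p·tᵢ + (1 − p)·tᵤ), with tᵢ and tᵤ the attendance of infected and uninfected students. If tᵢ = tᵤ in each arm, the observed prevalence is p: the 80% v 50% example gives 10% v 10%, RR 1.0. Otherwise, with true RR 0.80 (8.24% v 10.3%):

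- UCM tᵢ 80%, tᵤ 40%; UniLicungo 40% for both: 15.2% v 10.3%, RR 1.48.
- UCM 60% for both; UniLicungo tᵢ 60%, tᵤ 35%: 8.2% v 16.4%, RR 0.50.

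The bias can go either way.

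**4. Does the pre-post control remove it?** On the denominator of step 2, the ratio of change in the two arms equals the true ratio of change × (t after / t before at UCM) / (t after / t before at UniLicungo). The last factor cancels only if testing changes in the same proportion in both arms. Suppose prevalence is 10% throughout and testing is 50% everywhere except 80% at UCM at follow-up. UCM goes from 5% to 8% and UniLicungo stays at 5%, so the ratio of change is 1.6. The bias passes through in full.

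**5. Expected new infections.** With 343 per arm, all tested and all negative at baseline (both favourable), there are 343 × 0.5 = 171.5 person-years per arm. At an assumed 1, 2 or 3 per 100 person-years this gives 1.7, 3.4 or 5.1 infections. At 3.43 in each arm, the 95% limits around a rate ratio of 1 are exp(±1.96 × √(2/3.43)) = 0.22 to 4.5.

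**6. Power for prevalence if all 343 per arm were tested, clustering ignored.**

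| UniLicungo prevalence | Power, true RR 0.8 | Power, true RR 0.5 |
|---|---|---|
| 2.2% | 6.1% | 20.3% |
| 10.3% | 15.1% | 71.5% |
| 16.3% | 22.5% | 90.5% |

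Only a halving at the higher prevalences would be seen reliably.

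**The case against.** **The arms may be tested alike.** Consultations are announced every 3 months for the cohort. Step 4 provides the same service at UniLicungo on 3 days a week. Every participant gets an identification card and a recommendation to attend, and UniLicungo students are also prompted by teachers and the research team. Step 5 can even be read as placing sensitizing activities at both universities, though the design paragraph says otherwise. This stands in part: with near-complete and similar attendance, the bias would be small. But no section requires attendance, equal availability is not equal uptake, and hypothesis (c) predicts a difference.

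**Infection is not the primary outcome.** This stands. The design paragraph names (determinants of) behaviour change as primary, and the sample size serves that.

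**Denominators and missing tests belong in a fuller plan.** This also stands, and their absence is not the point. The point rests on what the article fixes: the data source, voluntary attendance, an effectiveness hypothesis and a general assurance on bias.

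**Stronger readings that the document does not support.**

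- A reader might infer that the programme is bound to look harmful. That needs untested students to be counted as negative, which the article does not say.
- Because "all students, no matter their STI/HIV state, will be enrolled in the cohort", a reader might infer that no reduction can be shown. In a fixed cohort, HIV prevalence within an arm cannot fall except through selective loss. But Table 2 also lists incidence, syphilis and symptoms, and a smaller rise than in the control arm would be a relative benefit.
- A reader might infer a single pooled indicator dominated by symptoms. The indicator cell is ambiguous, the question beside it lists the items one by one, and nothing shows that symptoms would dominate.

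**Conclusion.** The concern holds, confined to hypothesis (b) and the question on prevalence and incidence. Detection depends on voluntary attendance, the programme aims to raise attendance at UCM, and the pre-post control does not remove a difference that arises after baseline.

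The size depends on testing shares that the document does not give. Counting untested students as negative, 80% v 50% testing produces a relative risk of 1.6 from no effect. Among tested students, a true relative risk of 0.80 appears as anything from 0.50 to 1.48 in the examples shown, and is unbiased only if attendance is unrelated to infection or selection is alike in both arms. About 2 to 5 new infections per arm, on an assumed incidence of 1 to 3 per 100 person-years, would leave the rate ratio very imprecise even with complete testing.

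It would go too far to say that hypothesis (b) could never be addressed: near-complete and similar testing would remove most of the bias, though not the imprecision. As written, the plan does not secure that testing, so an effectiveness conclusion on transmission is not supported. The primary comparison of behaviour and its determinants is untouched.

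**What to change.** 1. **Denominator.** In Table 2, use tested students as the denominator for infection outcomes. Count HIV and syphilis incidence only among students negative at baseline who have a follow-up test.
2. **Reporting.** Report HIV, syphilis and symptoms separately. Beside each estimate, give the number and share tested, by university and time point.
3. **Hypothesis (b).** Restate it as a descriptive monitoring aim, in line with the wording of the cohort aims, and make no effectiveness claim on cyclical transmission. This step is essential, because step 1 still selects on attendance and so does not remove the bias.
4. **Discussion.** State that the control-group pre-post approach does not address differences in testing caused by the programme.

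Weighting by the probability of being tested can be added as a sensitivity analysis. It corrects only for measured predictors of attendance, so it should not be the main defence.

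**Cost.** Changes to wording and reporting, a smaller analysed set for infection outcomes, and the loss of one effectiveness claim. The sample size and the behavioural analysis stay as they are.
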